**For the Preconception Period:**

The primary objective of this trial is to evaluate the impact of the intervention on the diet quality of women measured with the Canadian Healthy Eating Index at 2, 4, and 6 months of follow-up.The secondary objectives of the preconception period are to evaluate the impact of the intervention on:- Urinary metabolomic indicators of women's dietary exposure at 2 months follow-up,- The diet quality of male partners at 2, 4, and 6 months follow-up,- The other lifestyle habits of women and their partners at 3 and 6 months (physical activity, sleep quality, anxious and depressive symptoms, and quality of life),- The anthropometric measures of women and their partners at 3 and 6 months (weight, waist circumference, and body fat percentage), and- The proportion of women and partners with a weight loss of at least 5% body weight at 3 and 6 months.

After completion of the primary outcome assessment, women and their partners who have achieved a pregnancy within 12 months following enrolment will be followed until the end of the pregnancy. Although, there is a potential for unbalanced study groups if the intervention has an impact on fertility, this exploratory follow-up phase will provide preliminary data on the impact of the intervention on lifestyle and clinical outcomes in pregnancy.

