### Variables and Data Collection

Participants' medical history and socioeconomic status will be evaluated at baseline. Women and their partner's diet quality will be measured with 24-h dietary recalls at baseline, 2, 4, and 6 months in preconception and at 6–8 weeks, 24–26 weeks, and 32–34 weeks in pregnancy. Women will provide urinary samples for the metabolomic analysis at baseline and 2 months in preconception and at 24–26 weeks in pregnancy. Women and their partner's other lifestyle indicators (physical activity, sleep, anxious, and depressive symptoms, quality of life, and attitude toward behavior change), and anthropometric outcomes will be evaluated at baseline, 3 and 6 months in preconception and every trimester in pregnancy. Information on pregnancy and neonatal outcomes will be collected from participants' medical records at the end of the study. The study variables, measuring tools, and the timing of data collection have been summarized in Table 1.

**Table 1 T1:** Summary of study variables.

		**Timing of data collection in preconception (months)**					**Timing of data collection in pregnancy (weeks of amenorrhea)**			
**Variables**	**Measuring Tool**	**0**	**2**	**3**	**4**	**6**	**6-8**	**24-26**	**32-34**	**End of study**
Medical history	Homemade questionnaire	•								
Socioeconomic status	Homemade questionnaire	•								

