**Lifestyle habits**										
Diet quality	C-HEI 2007 score measured with the R24W	•	•		•	•	•	•	•	
Diet quality	Urine dietary exposure biomarker profile	♀	♀					♀		
Physical activity	IPAQ	•		•		•	•	•	•	
Active minutes and step count	7-day Fitbit recording	•		•		•	•	•	•	
Sleep quality	PSQI	•		•		•	•	•	•	
Anxious and depressive symptoms	HADS	•		•		•	•	•	•	
Quality of life	SF-12	•		•		•	•	•	•	
Attitude toward behavior change	Homemade questionnaire	•		•		•	•	•	•	

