**Anthropometric measures**										
Height	Stadiometer	•								
Weight	Calibrated scale	•		•		•	•	•	•	
Body fat percentage	Foot to foot bioimpedance	•		•		•				
Waist circumference	Measuring tape	•		•		•				

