#### Secondary Outcome Analysis

For the main secondary outcome for the pregnancy phase of the trial, we will use a Chi-squared test to compare the proportion of women who have an adequate gestational weight gain in each group.

For the targeted analysis of urine biomarkers, the concentration of around 40 metabolites will be compared between baseline, 2 months in preconception and 24–26 weeks of pregnancy using repeated measures ANOVA or Friedman test with a Bonferroni adjustment for multiple comparisons. The correlation between the metabolite derived diet quality score and the C-HEI score will be evaluated using Pearson's correlation.

Although our sample size is fairly small, an exploratory multivariate analysis of non-targeted metabolome profiles will be realized using both unsupervised ‘natural clustering’ analysis and Supervised Random Forest classification.

For the other secondary outcomes, continuous variables will be assessed using Student's *t*-tests or Mann-Whitney tests as appropriate. Dichotomic variables will be analyzed using Chi-squared tests or Fisher's exact test as appropriate.

For participants who achieve a pregnancy prior to the 2-month food recall and/or 3-month preconception visit, lifestyle and anthropometric outcomes at the first pregnancy visit will be used to complete the preconception analysis. Women will be able to signal the occurrence of a pregnancy through the mobile application as soon as a period is missed. The application software will immediately notify the research team which will allow completion of data collection prior to the occurrence of significant pregnancy symptoms such as hyperemesis.

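### Women who conceive before the 2-month urine collection have no 2-month value and no substitute, and for women's waist and body fat the text and Table 1 disagree on whether a substitute exists

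*Protocol article*

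**What the plan says.** The substitution rule is in the last paragraph of Secondary Outcome Analysis in the protocol article. Its trigger is "For participants who achieve a pregnancy prior to the 2-month food recall and/or 3-month preconception visit", and its content is that "lifestyle and anthropometric outcomes at the first pregnancy visit will be used to complete the preconception analysis". Table 1 places the first pregnancy visit at 6–8 weeks. The same paragraph adds that a missed period reported in the application alerts the team at once, so that data collection can be completed early.

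Urine is scheduled in Variables and Data Collection: "Women will provide urinary samples for the metabolomic analysis at baseline and 2 months in preconception and at 24–26 weeks in pregnancy". Table 1 agrees. It lists "Urine dietary exposure biomarker profile" under the lifestyle habits heading, marked for women at 0 and 2 months and at 24–26 weeks only. The corresponding preconception objective, first in the list of secondary objectives, is "Urinary metabolomic indicators of women's dietary exposure at 2 months follow-up". The planned urine analysis compares baseline, 2 months and 24–26 weeks by repeated-measures ANOVA or Friedman test.

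For body size, the preconception objectives name weight, waist and body fat at 3 and 6 months for women and partners. Variables and Data Collection says that anthropometric outcomes of both are assessed every trimester in pregnancy. Table 1 marks weight ("Calibrated scale") at 6–8 weeks. It shows no mark for women in any pregnancy column for body fat ("Foot to foot bioimpedance") or waist ("Measuring tape"). The pregnancy objectives list waist and body fat for partners only.

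**The concern.** The rule points to a visit at which one of the preconception outcomes is not measured and two others may not be. The 2-month sample is the only preconception urine set after baseline. The Discussion presents urine profiling as objective and free of recall bias, and names urine samples when it addresses the lack of masking. If early conceivers have no value, the 2-month comparison is made only among women not yet pregnant at that point. Conception happens after randomisation, and the Objectives section accepts that groups could become unbalanced if the intervention affects fertility. The Discussion criticises an earlier preconception trial for measuring its primary outcome in pregnancy after randomising in preconception. A milder form of that selection would enter here for a secondary outcome. The comparison of the metabolite score with the C-HEI would also lose these women, because their C-HEI can be completed at 6–8 weeks and their urine cannot.

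**Working it through.** **1. Rule against schedule, for women who conceive early**

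| Outcome | Preconception time at issue | Measured in women at 6–8 weeks? | Can the rule be applied? |
|---|---|---|---|
| C-HEI (primary) | 2 months | Yes (Table 1) | Yes |
| IPAQ, Fitbit, PSQI, HADS, SF-12, attitude | 3 months | Yes (Table 1) | Yes |
| Weight | 3 months | Yes (text and Table 1) | Yes |
| Urine biomarkers | 2 months | No (text and Table 1) | No |
| Waist, body fat | 3 months | Text: every trimester. Table 1: no mark for women | Unclear |

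The symbol lost from the extracted table marks partner-only entries. Blank pregnancy cells for waist and body fat may therefore hold partner entries, which would fit the pregnancy objectives. That does not change what Table 1 shows for women.

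**2. Consequence for the planned urine test.** In their standard form, repeated-measures ANOVA and the Friedman test need a value at every time point. A woman who conceives before month 2 can have baseline and 24–26-week samples and still be dropped for lack of the middle one.

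**3. The plan's own sample size.** Inputs from Sample Size Calculation: difference 10 (read as points on the 100-point score), SD 13, alpha 5% (taken as two-sided), power 80%.

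n per group = 2 × (1.960 + 0.842)² × (13/10)² = 2 × 7.85 × 1.69 = 26.5, so 27. With 20% attrition, 27/0.8 = 33.75, so 34 per group and 68 in total. The figure reproduces. It rests on the C-HEI, which is collected at 6–8 weeks, so this point does not touch it.

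**4. How many women could be affected.** The protocol gives no conception rate. With an assumed constant monthly probability f from enrolment, the share conceiving before month k is 1 − (1 − f)^k.

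| f (assumed) | Before month 2 | Of 68 | Before month 3 | Of 68 |
|---|---|---|---|---|
| 5% | 1 − 0.95² = 9.8% | 7 | 1 − 0.95³ = 14.3% | 10 |
| 8% | 1 − 0.92² = 15.4% | 10 | 1 − 0.92³ = 22.1% | 15 |
| 12% | 1 − 0.88² = 22.6% | 15 | 1 − 0.88³ = 31.9% | 22 |
| 15% | 1 − 0.85² = 27.8% | 19 | 1 − 0.85³ = 38.6% | 26 |

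The month-2 columns apply to urine. The month-3 columns apply to waist and body fat, and only if Table 1 is the operative schedule. The counts are before attrition. For any given f they are upper figures, for two reasons. Eligibility asks only for intent to conceive within 12 months, so some women need not be trying at first. A woman who conceives just before month 2 may also give her scheduled sample before she knows.

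**The case against.** A reader might infer that the rule is unworkable for urine, waist and body fat alike, and that early conceivers go unscored by design. The documents do not support that. The text says that women's anthropometric outcomes are assessed every trimester, and on that reading first-trimester waist and body fat exist. The firm statement for these two is a conflict between text and table. The primary outcome, weight and the questionnaires can all be filled at 6–8 weeks, and women who conceive between months 2 and 3 keep their 2-month urine.

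It can also be said that the rule was never meant for urine. Its trigger names the food recall and the 3-month visit, and urine analysis has its own paragraph. Urine does sit under lifestyle habits in Table 1, so the scope is ambiguous. But if urine is outside the rule, the 2-month gap remains with no substitute at all.

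The missed-period alert is stated to allow data collection to be completed, without limiting which measures, so the team may already intend to take the urine then. That stands as a mitigating point, but neither schedule names it.

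Finally, the metabolite-derived score is described as exploratory, and an article may leave missing-data handling to a fuller plan. That lowers the weight. It does not settle the collection schedule, because a sample not taken cannot be recovered at analysis.

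**Conclusion.** The point holds for urine: the rule has no 6–8-week sample to draw on, and the stated test drops women without a 2-month value, so inclusion depends on conception after randomisation. For women's waist and body fat the finding is narrower: the text and Table 1 contradict each other, and until they are reconciled nobody can tell whether the rule can be applied.

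At assumed conception rates of 5–15% per month, about 10–28% of women (7–19 of 68) would be affected for 2-month urine. About 14–39% (10–26 of 68) would be affected for month-3 waist and body fat if Table 1 governs. Both ranges rest wholly on the assumed rates and on all women trying from enrolment, so they are approximate upper figures for those rates. The direction and size of any bias cannot be derived from the protocol. The primary outcome and the sample size are not affected.

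**What to change.** 1. In Variables and Data Collection and in Secondary Outcome Analysis, state that any outstanding 2-month urine set (the same three spot samples) is collected when the application signals a missed period.
2. Analyse that set at its actual time since randomisation, with a pregnancy indicator, in a model that keeps women with incomplete time points, such as a linear mixed model (on transformed concentrations if needed), in place of the complete-series ANOVA or Friedman test.
3. Reconcile the every-trimester statement with Table 1 for women's waist and body fat.
4. List by name the outcomes that the substitution rule covers, and say how month-3 waist and body fat are handled for early conceivers if they prove not to be measured in pregnancy.

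The cost is a small amendment. The urine set is brought forward, not added, and the alert already exists. The downside is that some samples will come from very early pregnancy or from before month 2, which is why actual time and pregnancy status belong in the model. Items 3 and 4 are wording changes, unless reconciliation adds measurements at pregnancy visits.

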### Interventions

#### Intervention Arm

Participants randomized to the intervention group will receive the *Healthy for my Baby* intervention. This intervention is based on the Control Theory, according to which behavior can be regulated by engaging oneself in an active process centered on establishing and following-up specific goals (51). Couples will initiate the preconception intervention by participating in a 60-min motivational interview (MI) session on healthy lifestyle habits (52). At the end of this session, each member of the couple will have set specific SMART lifestyle goals (53) in at least two of five key areas: nutrition, physical activity, sleep, well-being (stress, anxiety), and environment (tobacco use, drug use, alcohol consumption, or other toxic substances). Lifestyle goals will be tailored to each participant based on the priorities verbalized in the motivational interview with the aim of improving compliance with Canadian guidelines for diet, physical activity, sleep, and consumption of alcohol (54, 55). Participants will then have access to a mobile phone application designed by our research team that will help them achieve three goals in different dimensions at a time through daily self-monitoring (Supplementary Figure 1). Self-monitoring has been shown in a meta-regression analysis to be the most effective behavior change strategy to improve diet and physical activity (56). In addition to allowing participants to track their lifestyle goals, the mobile application includes references on healthy habits for preconception and pregnancy, a research visit calendar, a fertility tracker, links to videos on different aspects of parenthood, and a platform to contact the research team.

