One month after enrolment, couples will participate in a second 30-min MI to reevaluate their objectives and help resolve potential obstacles. They will also be invited to set new SMART goals in three of the five key areas. Participants will continue to have access to the mobile application for the remainder of the preconception follow-up. The research team will have access to the information entered in the mobile application and will use this data to determine if the intensity of the intervention needs to be increased. Participants who successfully reach their lifestyle goals will not have any further in-person meetings in the preconception period. Those who fail to meet their lifestyle goals will be contacted for further support and will be invited to participate to a maximum of two additional monthly motivational interview sessions by videoconference. Participants will have the option to track their weight in the mobile application and will be contacted for further support if weight gain is reported. Several reminders have been embedded in the application to improve adherence to the intervention. The research team will also be able to detect participants who are not using the application on a regular basis to contact them for further support.

If the woman becomes pregnant, the application will be put in pregnancy mode and participants will be invited to engage in two additional 30-min MI sessions at 6–8 and 10–12 weeks of gestation. The aim of these additional encounters is both to intensify the intervention in the critical period of early pregnancy and to tailor the lifestyle goals to the symptoms of pregnancy. Participants will keep using the mobile application for self-monitoring throughout pregnancy and up to three additional monthly videoconference meetings will be planned for those requiring further support according to data derived from the application.

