#### Control Arm

Participants randomized to the control group will receive standard advice on healthy lifestyle habits as provided by their usual care provider. Usual care in preconception is the same as that of healthy adults and does not specifically involve access to lifestyle interventions. In the Estrie region, which includes the Sherbrooke area, individuals with obesity, or overweight and a cardiometabolic diagnosis, have access to a free-of-charge program at local health centers, which includes group sessions with a limited individual nutritional intervention. However, these services are neither integrated nor targeted at preconception care and are rarely used by these couples. Participation in these sessions, or in any other lifestyle programs or consultations with a lifestyle professional will be documented. In addition to routine obstetrical care, women with GDM are typically followed by a nutritionist, and those who present comorbidities such as hypertension or morbid obesity may be followed by a nutritionist. Participants in this group will have access to a simplified version of the mobile application containing only the research visit calendar, the fertility tracker, videos on parenthood, and the platform to contact the research team. This version of the application does not contain any information on healthy lifestyle habits.

Participants from both study groups will be allowed to participate in the existing local *Taking Care of your Health* educational program if they are eligible or to consult any health care professional if clinically required. However, they will be asked not to voluntarily begin a similarly intense lifestyle program during the trial.

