#### Fertility Outcomes

The clinical pregnancy rate, spontaneous abortion rate, and the live birth rate will be compiled from the patient medical records.

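### Pregnancy is notified by a voluntary app signal while contact is unequal by arm, so early-loss counts, and less so clinical pregnancy counts, risk differential detection

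*Protocol article*

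**What the plan says.** **How the team learns of a pregnancy.** The Secondary Outcome Analysis section states: "Women will be able to signal the occurrence of a pregnancy through the mobile application as soon as a period is missed". The stated purpose is timing of assessments: "The application software will immediately notify the research team which will allow completion of data collection prior to the occurrence of significant pregnancy symptoms". The sentence covers both arms and describes something women may do, not a scheduled check.

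**Contact in the intervention arm (Intervention Arm section).** The app is meant to "help them achieve three goals in different dimensions at a time through daily self-monitoring". Reminders are built in, and "The research team will also be able to detect participants who are not using the application on a regular basis to contact them". Once a woman is pregnant, "participants will be invited to engage in two additional 30-min MI sessions at 6–8 and 10–12 weeks of gestation", with up to three further monthly videoconferences for those who need them.

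**Contact in the control arm (Control Arm section).** "Participants in this group will have access to a simplified version of the mobile application". It holds a visit calendar, a fertility tracker, videos and a platform for contacting the team. No daily task and no follow-up of non-users is described.

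**Schedule common to both arms (Variables and Data Collection, Table 1).** Preconception assessments fall at 0, 2, 3, 4 and 6 months; pregnancy assessments at 6–8, 24–26 and 32–34 weeks. The Objectives section follows couples who conceive within 12 months of enrolment and calls this phase exploratory.

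**Source of the outcomes (Fertility Outcomes section).** "The clinical pregnancy rate, spontaneous abortion rate, and the live birth rate will be compiled from the patient medical records". Table 1 places them at the end of the study. The objectives for pregnancy name the *viable* pregnancy rate; Table 1 and the Fertility Outcomes section name the *clinical* pregnancy rate.

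**The concern.** The trial is open label and compares pregnancy, spontaneous abortion and live birth rates between arms. The only notification route described depends on the woman opening the app and choosing to signal, and the arms are described as using the app to very different degrees. The difference continues after conception. Beyond the common 6–8-week assessment, a control woman has no scheduled contact until 24–26 weeks, whereas an intervention woman is invited at 10–12 weeks. In months 6 to 12 neither arm has a scheduled preconception assessment, so knowledge of a conception rests on the signal or on unscheduled contact.

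If early losses come to light more often in the intervention arm, its recorded spontaneous abortion rate rises with no true difference. In a small trial that could be read as harm. The recorded pregnancy rate, which the Discussion also lists as a feasibility measure, would rise slightly too. A woman who signals late may also miss the 6–8-week assessment. That assessment stands in for missing preconception data when conception precedes the 2-month recall or 3-month visit.

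**Working it through.** **1. The plan's own figures.** The article gives no expected conception, loss or detection rate. Only the arm size can be taken from it. The stated sample size reproduces: 2 × (1.96 + 0.84)² × 13² / 10² ≈ 26.5, so 27 per group; 27 / 0.80 = 33.75, so 34 per group and 68 in total. This is used below only as 34 women per arm.

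**2. Where the described contact differs by arm.**
- Months 0–6: assessments are equal; app use and follow-up of non-users are not.
- Months 6–12, not pregnant: no scheduled assessment in either arm; app use still differs if it continues.
- 6–8 weeks: an assessment in both arms, plus a session in the intervention arm.
- 10–12 weeks: a session in the intervention arm only.

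The sessions follow a pregnancy that is already known. They can bring a loss to light but cannot reveal more conceptions.

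**3. Illustration.** All inputs except 34 per arm are assumptions. Let *c* be the true conception rate (50–70%), *l* the true share of conceptions lost (15–25%), and *d* the share of losses that reach the record (95% in the intervention arm; 85%, 70% or 50% in the control arm). True rates are equal in both arms and every ongoing pregnancy is found.

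- Recorded pregnancy rate = c(1 − l) + c·l·d, so the false difference = c·l·(d_I − d_C).
- Loss rate per recorded pregnancy = l·d / (1 − l + l·d).
- False difference in recorded losses = 34·c·l·(d_I − d_C).
- Live birth per woman randomised = c(1 − l), which does not contain *d*.

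| l | d_C | Loss rate, intervention | Loss rate, control | Difference (points) | Pregnancy-rate difference, c = 50% to 70% (points) | Extra losses, c = 50% to 70% |
|---|---|---|---|---|---|---|
| 15% | 85% | 14.4% | 13.0% | 1.3 | 0.75 to 1.05 | 0.3 to 0.4 |
| 15% | 70% | 14.4% | 11.0% | 3.4 | 1.9 to 2.6 | 0.6 to 0.9 |
| 15% | 50% | 14.4% | 8.1% | 6.2 | 3.4 to 4.7 | 1.1 to 1.6 |
| 25% | 85% | 24.1% | 22.1% | 2.0 | 1.25 to 1.75 | 0.4 to 0.6 |
| 25% | 70% | 24.1% | 18.9% | 5.1 | 3.1 to 4.4 | 1.1 to 1.5 |
| 25% | 50% | 24.1% | 14.3% | 9.8 | 5.6 to 7.9 | 1.9 to 2.7 |

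Differences are taken before rounding. Example from the last row: 0.25 × 0.95 / (0.75 + 0.2375) = 24.1% against 0.25 × 0.50 / (0.75 + 0.125) = 14.3%.

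Live birth per woman randomised differs by 0 in every row. Live birth per *recorded* pregnancy does not: in the last row it is 0.75/0.9875 = 75.9% against 0.75/0.875 = 85.7%. With equal detection every difference is 0.

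**4. Set against chance.** With c = 60% and l = 25% there are 34 × 0.60 = 20.4 conceptions per arm. The standard error of a difference in loss rate is then √(2 × 0.25 × 0.75 / 20.4) = 0.136, or about 14 points. Even the largest false difference in the table is smaller than that.

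**The case against.** The strongest reply is that the app does not define these outcomes. They come from medical records at the end of the study, with no arm difference stated, and the signal exists to time data collection. A loss known only to the study team, with no record, would enter the endpoint in neither arm. This stands in large part. Unequal contact matters only through a further step, such as a staff contact that leads to a clinical visit, or a known pregnancy that prompts a closer record search. The article does not describe such a step, but it does not say that records are searched alike for every randomised woman either.

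Control women also have the app, with a fertility tracker and a contact platform, and share the month 2 to 6 assessments and the 6–8-week assessment. This stands and narrows the gap.

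A condensed article may leave a scheduled pregnancy check to the full protocol. That is fair, and the missing detail alone would not be a finding. The point rests on the unequal contact that the article does describe.

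A reader might go further and infer that the fertility outcomes *are* biased, or that the extra sessions uncover more conceptions. The documents support neither. The record-based source makes bias a possibility only, the sessions come after a pregnancy is known, and live birth per woman randomised hardly depends on finding early losses.

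**Conclusion.** The point holds as a risk, not as demonstrated bias. Contact differs by arm in a way that could make early losses more visible in the intervention arm. The spontaneous abortion rate is the measure most exposed; the clinical pregnancy rate and timely entry into pregnancy follow-up are exposed less. Live birth per woman randomised is little affected.

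The size cannot be taken from the documents. The range of about 1 to 10 points, or fewer than 3 losses per arm, rests wholly on the assumed conception, loss and detection rates and would be 0 if detection were equal. Priority is low: these are exploratory secondary outcomes, and the trial is powered on diet quality. It is still worth settling early, because unequal ascertainment is hard to repair once data collection has ended.

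**What to change.** - Send both arms the same automated pregnancy query on one schedule from randomisation to 12 months, with the same follow-up of non-responders. E-mail is already used for the dietary recalls.
- Send one outcome query at about 12 weeks of gestation in both arms.
- Review medical records in the same way for every randomised woman, whether or not a pregnancy was signalled.
- Use all randomised women as the denominator, and name live birth per woman randomised as the fertility comparison least exposed to detection.
- Reconcile *viable* pregnancy (objectives for pregnancy) with *clinical* pregnancy (Table 1 and Fertility Outcomes). The definition affects how far early losses enter the rate.
- Keep every pregnancy learned through the app in the comparison. Leaving them out would discard true events, probably more in one arm. At most, record how each pregnancy was first learned and report a sensitivity analysis by that route.

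The cost is an automated message, one short query and some protocol wording. The downside is a slight added burden on participants and a little more contact in the control arm.
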